### Measurements

The baseline characteristics of all participants including gender, age, body height, body weight (BW), abdominal circumference, office blood pressure (BP), pulse rate (PR), duration of T2DM, complications, background treatment, and smoking habit will be recorded prior to randomization. The background treatment and trial medication and adherence will be recorded for each patient at each visit. Abdominal circumference, BW, BP, and PR will be measured at baseline and at 24 weeks. The following assessments and methodology will be also applied at baseline and at 24 weeks: peripheral endothelial function according to the RH-PAT test, echocardiography (left ventricular ejection fraction determined by a modified Simpson method, left atrial volume index, E, septal e’, lateral e’, and E/e’ by tissue Doppler imaging), and non-contrast abdominothoracic computed tomography (CT) to measure pericardiac, hepatic, and perirenal fatty tissue, renal size, and blood and urine samples. (Please see Additional file 1). Certain serum biomarkers including *N*-terminal pro-brain natriuretic peptide, erythropoietin, cystatin C, and procollagen III peptide will also be measured at the central laboratory of SRL Inc., Tokyo, Japan. Images of non-contrast abdominothoracic CT will be measured at the core laboratory of the Department of Diabetes, Endocrinology, and Metabolism, Fukushima Medical University, Fukushima, Japan.

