### Trial endpoints

The primary endpoint in this trial is the change in natural log-transformed RHI (LnRHI) from baseline to 24 weeks or discontinuation. The secondary endpoints include (i) the  % change in LnRHI from baseline to 24 weeks or discontinuation, (ii) the proportion of patients with clinically meaningful changes in LnRHI (≥ 15% increase from baseline at 24 weeks or discontinuation), (iii) the proportion of patients with clinically meaningful improvement in RHI (≥ 2.10 at 24 weeks or discontinuation), (iv) the proportion of patients attaining (ii) and/or (iii), and (v) the proportion of patients with clinically meaningful changes in LnRHI (≥ 15% decrease from baseline at 24 weeks or discontinuation). Additional efficacy endpoints include changes from baseline to 24 weeks or discontinuation in (i) blood and urine laboratory values (Additional file 1), (ii) vital signs including abdominal circumference, BP, PR, BW, and body mass index, (iii) vascular functional parameters (AI, HRV, SDNN, and LF/HF) measured by a RH-PAT device, (iv) left ventricular systolic and diastolic function measured by echocardiography, and (v) pericardiac, hepatic, and perirenal fatty tissue and renal size measured by non-contrast abdominothoracic CT.

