### Statistical considerations

#### Sample size estimation

The effects of SGLT2is on peripheral endothelial function remain to be elucidated as the currently available evidence is very limited. Sugiyama et al. [38] used RH-PAT to assess the effects of the SGLT2 inhibitor dapagliflozin on endothelial function in Japanese patients with uncontrolled T2D (baseline HbA1c, 7.9%; baseline eGFR, ~ 74 mL/min/1.73 m^2^; unknown cardiovascular event history). The sample size was estimated to detect mean differences of 0.15 and 0.05 in the change in LnRHI for the dapagliflozin and non-SGLT2 inhibitor group, respectively. The estimated group difference was 0.10, the standard deviation was 0.15, the power was 90%, and the two-sided α was 0.05. As a result, 6 mo of dapagliflozin treatment significantly improved endothelial function. The actual difference between the dapagliflozin and non-SGLT2 inhibitor groups in terms of LnRHI was 0.139. On the other hand, the aim of the present trial is to evaluate the effects of ipragliflozin on the aforementioned endpoint in patients with CKD. Compared to those in the study population of Sugiyama et al., these individuals may present with more advanced cardiovascular damage that is difficult to ameliorate using the available interventions. Thus, we estimated a difference of 0.10 ± 0.15 between the groups in terms of the change in LnRHI. At α = 5% for a two-sided test, a sample size of 98 patients was needed to provide a power of 90% for each comparison. Considering a potential dropout rate of 12%, it was estimated that ≥ 110 patients (55 patients per arm) would provide sufficient statistical power for the trial.

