#### Statistical analysis plan

Summary statistics will be used to calculate all baseline characteristics including the categorical variable frequencies and proportions and the normally distributed mean ± standard deviation or median [interquartile range] with skewed distribution for the continuous variables. Patient characteristics will be compared by Fisher’s exact test for categorical variables and the Wilcoxon rank sum test for continuous variables.

Analyses of the primary and secondary endpoints will be performed for the full analysis set (FAS). The FAS excludes all participants with no post-randomization efficacy endpoint data and those deemed ineligible after registration because they failed to provide informed consent or did not meeting the study eligibility criteria.

The primary endpoint was a comparison of treatment effects between treatment groups. The baseline-adjusted least-square means (LSM) and their 95% confidence intervals (CI) will be estimated by analysis of covariance (ANCOVA) for the FAS. For a secondary analysis of the primary endpoint, an analysis of variance including allocation factors and treatment group as factors will also be performed. As a supplementary analysis, the primary endpoint will also be analyzed in the per protocol set excluding subjects seriously violating the trial protocol. Prespecified subgroups stratified according to clinical characteristics based on, but not limited to, the RHI at baseline (< 1.67 or ≥ 1.67) will be analyzed for the primary endpoint as described above.

For the secondary endpoints, (i) the % change in LnRHI from baseline to 24 wks or discontinuation will be analyzed by a two-sample *t* test. Their LSMs and 95% CIs will be calculated and the treatment effects will be compared between groups. (ii) The proportions of patients presenting with clinically meaningful changes in LnRHI or RHI will be analyzed with a logistic regression model adjusted by the corresponding baseline values to calculate the odds ratios and their 95% CIs and compare the treatment effects between groups.

Changes in the additional efficacy endpoints from baseline to 24 weeks or discontinuation will be analyzed by ANCOVA as for the primary endpoint. The LSMs and their 95% CIs will be calculated and the treatment effects will be compared between groups. Pearson’s correlation coefficients will be used to identify the correlations between the changes in RHI from baseline and each of the additional efficacy endpoints.

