## Discussion

The PROCEED trial is an investigator-initiated, ongoing, prospective, multicenter, open-label, randomized-controlled clinical trial. Its purpose is to test the hypothesis that ipragliflozin is an effective therapy for T2D patients with established CKD and impaired endothelial function. The primary endpoint of the trial is the change in the peripheral endothelial functional parameter for the treatment group compared to the non-SGLT2is-use control group. This parameter will be measured by RH-PAT from baseline to 24 wks or discontinuation. Several cardiorenal and metabolic markers will also be investigated in this study. In this way, the potential mechanistic association between the changes induced by ipragliflozin treatment and endothelial function may also be evaluated. The present trial may provide novel insights into the pathological role of peripheral endothelial dysfunction in patients with T2D and established CKD and clarify the therapeutic role of ipragliflozin in this process.

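### The planned simple Pearson correlations between change in RHI and change in each marker carry no arm term, so a marker can appear linked to RHI only because ipragliflozin moved both

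*Protocol article*

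**What the plan says.** The Statistical analysis plan section of the article names the statistic, both variables and the purpose: Pearson "correlation coefficients will be used to identify the correlations between the changes in RHI from baseline and each of the additional efficacy endpoints". It mentions no arm term, stratification or partial coefficient. The same section does state adjustment for other models: ANCOVA for the primary endpoint and baseline-adjusted logistic regression for the responder endpoints.

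The variable in the correlation is RHI. The Trial endpoints section, however, puts the main outcome on the log scale: "The primary endpoint in this trial is the change in natural log-transformed RHI (LnRHI) from baseline to 24 weeks or discontinuation". The markers to be correlated cover five families, beginning with "blood and urine laboratory values (Additional file 1), (ii) vital signs including abdominal circumference, BP, PR, BW, and body mass index" and going on to vascular, echocardiographic and CT measures.

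The Discussion says what these data are for: "the potential mechanistic association between the changes induced by ipragliflozin treatment and endothelial function may also be evaluated". The legend to Fig. 1 also lists elucidating mechanisms as an aim.

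On the marker analyses themselves, the plan says: "Changes in the additional efficacy endpoints from baseline to 24 weeks or discontinuation will be analyzed by ANCOVA as for the primary endpoint". No transformation of the markers is mentioned. Skewness comes up only for baseline summaries, which use the "median [interquartile range] with skewed distribution for the continuous variables".

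**The concern.** A Pearson coefficient computed over both arms mixes two things: how far changes in RHI and in the marker go together among patients on the same treatment, and how far the two arm means differ. Only the first bears on whether a marker's change accompanies the endothelial change. The second restates two treatment effects that the ANCOVAs already estimate.

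The distortion is largest where the trial succeeds, because it needs a treatment effect on RHI. Many markers are to be correlated, each at p < 0.05, and the article applies no multiplicity adjustment. A pooled analysis could therefore yield several apparent links that say nothing beyond the fact that ipragliflozin changed both variables. At stake is the interpretation of an exploratory but declared aim. The efficacy comparison is not at stake.

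**Working it through.** **Inputs from the article.** Sample size estimation gives the planned effect: "we estimated a difference of 0.10 ± 0.15 between the groups in terms of the change in LnRHI". It also gives two-sided α = 0.05, power 90% and 98 patients. Allocation is 1:1 (Randomization), and the Discussion says a two-sample t-test was used for the sample size.

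**The plan's own figure.** By the normal approximation, n per arm = 2 × (1.960 + 1.282)² × (0.15/0.10)² = 47.3, so 48 per arm and 96 in total. The exact t-test needs 48.26, so 49 per arm and 98 in total, with power 90.4%. The stated 98 is reproduced, and 49 per arm is used below.

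**Assumed inputs.** The article gives no effect of ipragliflozin on any marker, so marker shifts from 0.5 to 2.0 within-arm SD are assumed. Within-arm correlation is set to zero, so every significant result is a false link. The planned effect is stated only for LnRHI and is taken to stand for the shift in RHI.

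**Formula.** Let dx and dy be the differences between arms in change, in within-arm SDs, for LnRHI and for the marker. With equal arms and zero within-arm correlation,

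pooled r = (dx·dy/4) / √[(1 + dx²/4)(1 + dy²/4)].

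With dx = 0.10/0.15 = 0.667 and dy = 1.0: numerator 0.667/4 = 0.1667; denominator √(1.1111 × 1.25) = 1.1785; r = 0.141.

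**Significance threshold.** At n = 98 (96 degrees of freedom, t = 1.985), |r| must exceed 1.985/√(96 + 1.985²) = 0.199.

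**Simulation.** 20,000 trials per scenario, 49 per arm, with normal changes independent within arm. The pooled Pearson test (96 df) is compared with the arm-adjusted partial correlation (95 df).

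| Marker shift (SD, assumed) | Expected pooled r | Pooled, p < 0.05 | Arm-adjusted, p < 0.05 |
|---|---|---|---|
| 0 | 0.00 | 5% | 5% |
| 0.5 | 0.08 | 12% | 5% |
| 0.8 | 0.12 | 21% | 5% |
| 1.0 | 0.14 | 29% | 5% |
| 1.5 | 0.19 | 47% | 5% |
| 2.0 | 0.22 | 61% | 5% |

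A marker that falls gives the same rates with a negative r. If ipragliflozin does not move LnRHI (dx = 0), the pooled rate is about 5% at every marker shift.

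**Sensitivity.** The article quotes a difference of 0.139 from the dapagliflozin study. With the SD kept at 0.15, dx = 0.139/0.15 = 0.927, and the pooled rates for shifts of 0.5, 0.8, 1.0 and 1.5 SD become 18%, 34%, 46% and 73%. Arm adjustment again gives about 5%.

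**Skewness, checked separately.** With log-normal marker changes (log-SD 0.5, 1.0, 1.5) and no arm effect, the false-link rate is 4.8% to 5.3%, so skewness alone creates no links. With arm effects on both variables (0.667 and 1.0 SD) the pooled rate is 29% to 48%, and arm adjustment returns it to about 5%. On efficiency, an assumed log-normal marker (log-SD 1.0 to 1.3, within-person log-SD 0.4 to 0.5, 30% reduction) gives raw-change ANCOVA 29% to 57% power against 71% to 90% on the log scale. Type I error of the raw analysis stayed at about 4% to 5%.

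**The case against.** The article does not say that the arms are pooled. It leaves detail to a statistical analysis plan, not shown here, to be confirmed before database lock, and whether an exploratory correlation is run overall or by arm could be settled there. This stands in part: a reader might infer that the plan rules out adjustment for arm, and the text does not go that far. But the article does more than stay silent. It fixes a statistic that takes no covariate, while naming adjustment for its other models, so pooling is the natural reading.

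A reader might also infer that markers moved by ipragliflozin will look linked to RHI. The figures do not support that. For shifts up to 1.5 SD the expected r stays below the 0.199 threshold and most trials would show no link. Both variables must move, and the Discussion itself calls prior clinical results on endothelial function partly inconsistent.

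A third tempting reading is that untransformed skewed markers add to the false links or make the confidence intervals invalid. Skewness creates no links by itself, type I error held, and no loss of coverage has been shown. The article names "pro-brain natriuretic peptide, erythropoietin, cystatin C, and procollagen III peptide will also be measured" but does not describe the distribution of these markers, and does not fix a raw scale for them either. What remains is a possible loss of power.

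Finally, the Discussion speaks only of a potential association that may be evaluated, and the additional endpoints rank below the primary and secondary ones. Both are true and limit the weight of the point. An arm-adjusted association would not prove mechanism either; it would only stop the treatment effect from being counted as association.

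**Conclusion.** The point holds as a conditional one. Read naturally, the planned correlation is pooled, and it can then declare a link between RHI and a marker when none exists within arms. This rests on pooling, on a real effect of ipragliflozin on both variables, on the planned 0.67 SD effect being achieved, and on the assumed marker shifts. Under those conditions the false-link rate is roughly two to nine times the nominal 5% for shifts of 0.5 to 1.5 SD (12%/5% = 2.4; 47%/5% = 9.4). Without a shift in either variable there is no inflation.

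The mismatch between RHI in the correlation and LnRHI in the primary endpoint stands on the text alone. The scale of skewed markers is a separate, lesser matter of efficiency that depends on distributions the article does not give. The change is worth making because mechanism is a declared aim and the remedy is nearly free.

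**What to change.** In the statistical analysis plan, before database lock:

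- Replace the simple Pearson correlation with a partial correlation, or a regression of change in LnRHI on change in the marker, adjusted for treatment arm and for the baseline values of both. Baseline belongs in the model because the Discussion itself presumes that change in LnRHI is negatively related to its starting level.
- Show the estimate within each arm beside the adjusted one.
- Use LnRHI throughout, to match the primary endpoint.
- Present the results as exploratory association, not as evidence of mechanism.
- As a secondary matter, state that markers found to be right-skewed will be analysed by ANCOVA on log values and reported as ratios of geometric means.

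The cost is a few sentences and slightly more programming. No new data are needed, and neither the sample size nor the primary analysis changes.

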### Trial organization and oversight (Additional file 2)

The principal investigator of the PROCEED trial is [name] of the Department of Cardiovascular Medicine at Saga University. The trial secretariats are located at the Department of Cardiovascular Medicine of Saga University and the Translational Research Center for Medical Innovation in Kobe, Japan. Data management, monitoring activities, statistical analyses, and audits will be independently implemented in compliance with an outsourcing agreement. Data monitoring will be enforced to ensure proper research performance. An independent audit team will inspect several main institutes to ensure trial data quality.

## Discussion

The PROCEED trial is an investigator-initiated, ongoing, prospective, multicenter, open-label, randomized-controlled clinical trial. Its purpose is to test the hypothesis that ipragliflozin is an effective therapy for T2D patients with established CKD and impaired endothelial function. The primary endpoint of the trial is the change in the peripheral endothelial functional parameter for the treatment group compared to the non-SGLT2is-use control group. This parameter will be measured by RH-PAT from baseline to 24 wks or discontinuation. Several cardiorenal and metabolic markers will also be investigated in this study. In this way, the potential mechanistic association between the changes induced by ipragliflozin treatment and endothelial function may also be evaluated. The present trial may provide novel insights into the pathological role of peripheral endothelial dysfunction in patients with T2D and established CKD and clarify the therapeutic role of ipragliflozin in this process.

Recent cardiovascular outcome trials (CVOTs) involving SGLT2is clearly and consistently associated SGLT2is with substantial reductions in cardiovascular and renal events in patients with T2D and at high risk for these complications. A systematic review and meta-analysis of the three first CVOTs (EMPA-REG OUTCOME, CANVAS Program, and DECLARE-TIMI 58) [11] disclosed that risk reduction provided by SGLT2is for major adverse cardiovascular events (MACE) was significant in a subgroup with a history of atherosclerotic cardiovascular diseases (CVD). However, SGLT2is did not significantly reduce these risks in a subgroup with multiple risk factors. Conversely, SGLT2is was associated with the reduction of risk of composite renal outcomes regardless of CVD history. Moreover, SGLT2is treatment significantly reduced the risk of the aforementioned adverse events in patients with decreased eGFR (< 60 mL/min/1.73 m^2^). Thus, SGLT2is may have renoprotective efficacy for a wide range of T2D patients. The CREDENCE trial was the first to investigate the effects of canagliflozin on composite renal outcome in patients with T2D and established CKD. It confirmed that canagliflozin treatment consistently reduced the development of primary renal composite outcome independent of CVD history and across baseline levels of markers of deteriorating renal function such as decreased eGFR and abnormal albuminuria [15, 39]. Renal benefits in T2D patients with concomitant CKD irrespective of baseline RAAS inhibitors were also reported in several subsequent studies [16, 40, 41]. Therefore, SGLT2is may have class and additive renal efficacy. Giugliano et al. [40] conducted a meta-analysis on data compiled from four CVOTs and found that SGLT2is was more effectively at preventing MACE in subgroups with reduced eGFR (< 60 mL/min/1.73 m^2^) than in those with preserved eGFR (≥ 60 mL/min/mL/1.73 m^2^). Hence, SGLT2is treatment may play an important therapeutic role in patients with T2D and CKD. Further, deteriorated renal function may be a clinically meaningful indicator of the cardiovascular and renal effects of SGLT2is treatment [18].

SGLT2is have multifactorial effects on non-glycemic parameters associated with primary glycosuria and natriuresis. SGLT2is modulates hemodynamics and remodels metabolism. In turn, these responses have cardiovascular and renal benefits [42, 43]. The most widely accepted mechanism of the renoprotective efficacy of SGLT2is is hemodynamically-mediated restoration of tubuloglomerular feedback [21–24, 44]. Several clinical and preclinical trials suggested that SGLT2is correct pathological interconnections between the heart and kidneys. They may be directly renoprotective by reducing inflammation and oxidative stress, attenuating hyperactivated sympathetic nervous systems, and improving vascular function [45, 46].

Endothelial function plays a vital role in maintaining vascular homeostasis but it can be impaired by various metabolic disturbances and systemic diseases [26]. Endothelial dysfunction is implicated in the initial steps of atherogenic change and subsequent atherosclerosis progression. It is associated with cardiovascular events and poor prognosis [27, 47, 48]. The intrarenal endothelium regulates renal microcirculation and its structures. Its dysfunction is also associated with renal damage and CKD progression [30, 31, 49, 50]. Thus, endothelial dysfunction may be linked to both T2D and CKD (Fig. 1). It is, therefore, expected that the cardiovascular and renal benefits of SGLT2is are mediated at least in part by the improvement of endothelial dysfunction, particularly in patients with T2D and established CKD.

Assessment of peripheral endothelial function may furnish clinically useful information on the present cardiovascular risk status, the future outcome, and the evaluation of treatment efficacy [51]. To date, several animal studies have already demonstrated that SGLT2is, including ipragliflozin, ameliorated endothelial dysfunction and vascular and kidney injuries [52–57]. Several clinical studies also investigated the effects of SGLT2is on endothelial function in diabetic patients with and without additional cardiovascular event risk factors [38, 58–64]. However, the results were partially inconsistent. In certain studies, SGLT2is conferred beneficial effects on vascular function in diabetic patients at relatively low risk of cardiovascular events. Nevertheless, there was no obvious effect of 6 months of SGLT2is treatment in patients with established CVDs [62, 63]. Thus, short-term interventions may be too brief to improve endothelial function in patient subpopulations whose vascular injuries are more advanced than those with no CVD history. In the CANVAS, DECLARE-TIMI 58, and CREDENCE trials on patients with T2D and established CKD, SGLT2is treatment consistently improved cardiac- and renal failure outcomes in patients receiving primary prophylaxis [15, 65, 66]. Therefore, SGLT2is may have a therapeutic impact on the cardiorenal axis even in the aforementioned patient subpopulation. Moreover, the improvement of endothelial dysfunction may play a mechanistic role in this process. To the best of our knowledge, however, no previous study has assessed the effects of SGLT2is on vascular parameters such as endothelial function in diabetic patients with established CKD. It has not yet been established whether the beneficial effects of SGLT2is on endothelial dysfunction constitute a mechanism for the robust improvement observed in the patient populations participating in the previous CVOTs. There are ongoing clinical trials testing the hypothesis that SGLT2 inhibitors prevent CKD progression in patients with pre-existing CKD [67, 68]. The present study may also furnish mechanistic insights into the renoprotective efficacy of SGLT2 inhibitors.

This trial had several limitations that were also inherent to similar earlier investigations performed by our study team [37, 69]. First, we did not use a double-blind placebo-controlled trial here but rather an open-label design. This configuration might create an unexpected bias towards assessing potentially subjective endpoints associated with the treatments selected by the investigators. This bias could occur despite the strict requirement that the background medications of all participants must not change throughout the study. Second, the trial sample size is relatively small and the study treatment period is comparatively short. Third, the ANCOVA is set as the primary analysis based on our preliminary presumption of a negative correlation between the LnRHI values and their changes from baseline. We did not establish the correlation coefficient required to calculate the sample size. Hence, we estimated the sample size via a conservative two-sample *t*-test. Fourth, although the RH-PAT examination is non-invasive, easy to perform, and operator-independent, its output is sensitive to individual physical conditions and the ambient environment. To minimize these influences across all participating institutions, investigators must perform the RH-PAT examination in accordance with the operating manual provided by the manufacturer. Further, the present study excludes patients with RHI ≥ 2.10 according to the RH-PAT test performed prior to randomization. This threshold was previously proposed for normal endothelial function. Its border zone was ≥ 1.6 and < 2.10 [32]. The widely accepted cutoff value of RHI is 1.67 for the discrimination of normal and abnormal endothelial function [36]. Thus, changes in RHI in response to the treatments in the present study may differ depending on the baseline level. Therefore, we will attempt to assess the relative impacts of these effects using subgroup analyses as the primary endpoints and responder/non-responder analyses as the secondary endpoints. Finally, as SGLT2is are pharmacologically active in the kidney, their glucose-lowering effect may be insufficient in patients with lower eGFR [70]. However, the renoprotective efficacy of SGLT2is may be independent of glycemic control [25]. At this time, ipragliflozin is not recommended in diabetic patients with severe renal dysfunction such as eGFR < 30 mL/min/1.73 m^2^. Therefore, the inclusion criteria of the present trial align with the official indications for ipragliflozin.

In summary, the PROCEED trial is the first to assess the effects of ipragliflozin on endothelial dysfunction in patients with T2D and established CKD. It is also intended to assess the potential effects of ipragliflozin on other cardiovascular and renal functional markers and the morphological changes in the pericardiac, hepatic, and perirenal fatty tissue and renal size measured by non-contrast abdominothoracic CT. It is believed that this trial will provide profound and novel insights into the putative underlying mechanisms of the renal benefits of SGLT2is in a patient population presenting with T2D and established CKD.

